### Exclusion Criteria

The exclusion criteria are as follows: (1) preexisting malignant tumors or other types of solid or nonsolid tumors; (2) disease progression or recurrence at the time of study enrollment; (3) heart rate (HR) exceeding 70% of the age-specific maximum or below 60 beats per minute, systolic blood pressure of >180 mm Hg or orthostatic hypotension, respiratory rate of >50 breaths per minute, body temperature of >37.5 °C, or oxygen saturation of <90%; (4) occurrence within 3 months before enrollment of cardiac insufficiency (New York Heart Association functional class II or higher), severe pulmonary function decline, fracture, hypertension of grade ≥2, or concurrent use of ≥2 antihypertensive medications; (5) history of HIV infection, active hepatitis B virus or hepatitis C virus infection, or uncontrolled systemic infection; and (6) major surgery within 4 weeks before enrollment or planned major surgery during the study period.

### Grouping and Masking

Participants with a clear preference for either intervention will be allocated accordingly, whereas those without a preference will be randomly assigned to the experimental or control group. This approach was adopted to accommodate the preferences of the participants and their guardians while preserving the benefits of randomization. Due to the nature of the intervention, participants and intervention providers will not be blinded to group allocation. However, outcome assessors and statisticians will remain blinded to group assignments to minimize bias.

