**Methods:**

A total of 68 participants will be recruited and allocated to 2 groups matched in age and gender, with consideration given to the preferences of participants and their guardians. The control group will receive standard in-hospital medical treatment and health education, whereas the experimental group will receive a 6-month digital therapy–based aerobic exercise intervention in addition to standard care. Outcomes will be assessed at baseline and 3 and 6 months, with data collected for analysis. The primary outcomes are the 6-minute walk distance and the timed scores (in seconds) for the timed up and go and stair climb tests. The secondary outcomes include body composition, grip strength, and quality of life measured using the Pediatric Quality of Life Inventory version 4.0.

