### Statistical Analysis

Data will be analyzed using SPSS (version 26.0; IBM Corp). Primary models using the intention-to-treat principle will be conducted for all primary and secondary outcomes. Data normality will be assessed initially. Nonnormally distributed data will be presented as medians with IQRs. Between-group comparisons (intervention vs control) for these variables will be conducted using the Mann-Whitney *U* test. Within-group comparisons (baseline vs each follow-up) will be conducted using the Wilcoxon signed rank test. Categorical data will be reported as numbers with percentages and analyzed using the chi-square test. Differences in primary and secondary outcomes between the intervention and control groups across all assessment time points will be evaluated using mixed-model analysis. Statistical significance will be defined as a *P* value of <.05, with multiple comparisons adjusted using the Bonferroni method.

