### Sample Size Calculation

The sample size was calculated using G*Power (version 3.1.9.7; Heinrich Heine University Düsseldorf). On the basis of a related study [32], an effect size of 0.953 was determined, derived from the difference in the 6MWD between the experimental group (mean 35.89, SD 8.46 laps) and the control group (mean 26.76, SD 10.57 laps) after the intervention. The significance level (α) was set at .05, and the power (1 – β) was set at 0.95. The calculation indicated that 30 participants were required for each group. To account for a potential 10% loss to follow-up, 34 participants per group were planned for recruitment, resulting in a total sample size of 68 participants.

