### Limitations

Despite its potential, this study has several limitations that should be considered when interpreting the results. First, the single-center design and small sample size restrict the generalizability of the findings. Future research should involve multiple centers across different regions and include larger samples to enhance external validity. Second, although outcome assessors and statisticians were blinded, participants and care providers were not. Furthermore, for participants with a preexisting preference, allocation was based on that preference rather than randomization. This nonrandomized allocation for a subset of participants introduces potential performance and expectation biases. As a preliminary investigation, this study provides foundational insights that can inform the design of a more rigorous randomized controlled trial in the future. Finally, the digital therapy platform and exercise programs are self-developed, and no formal large-scale usability testing was conducted before the intervention. While the design was informed by pediatric expertise and in-study engagement metrics supported feasibility, future iterations would benefit from structured usability testing to optimize the platform before broader implementation.

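### Self-selected and randomised children are pooled in one intention-to-treat comparison, so the effect estimate is open to confounding by self-selection, which the protocol does not name

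*Protocol article*

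**What the plan says.** Grouping and Masking sets the allocation rule: "Participants with a clear preference for either intervention will be allocated accordingly, whereas those without a preference will be randomly assigned" to one of the two groups. It justifies the rule in these words: "This approach was adopted to accommodate the preferences of the participants and their guardians while preserving the benefits of randomization".

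The abstract's Methods paragraph describes allocation differently. Participants are "allocated to 2 groups matched in age and gender, with consideration given to the preferences of participants and their guardians". It does not mention randomisation, and Grouping and Masking has no matching step.

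Statistical Analysis states: "Primary models using the intention-to-treat principle will be conducted for all primary and secondary outcomes". The between-group comparison is: "Differences in primary and secondary outcomes between the intervention and control groups across all assessment time points will be evaluated using mixed-model analysis". It mentions neither allocation route nor a separate look at the randomised children. Sample Size Calculation powers a single two-group comparison on all 68 children.

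Limitations acknowledges that children with a preference are not randomised and concludes: "This nonrandomized allocation for a subset of participants introduces potential performance and expectation biases". The abstract's Results paragraph and the Results section both expect the trial to demonstrate that digital therapy is effective.

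**The concern.** Random assignment makes the arms comparable on average in everything, measured or not. That holds for the children without a preference. It does not hold for those who choose. Families who opt for a daily home exercise programme lasting 24 weeks may differ from those who decline it in the child's fitness, fatigue, motivation or support at home. Any of these could affect the 6-minute walk, timed up and go and stair climb tests, all of which depend on effort.

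Intention to treat does not repair this. It keeps each child in the arm assigned, but if the child chose that arm, the comparison carries the choice with it. Blinded assessors limit detection bias, not selection.

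A pooled difference could therefore partly reflect who chose exercise, while the randomised evidence in the trial is not shown separately. The performance and expectation biases named in Limitations are different problems. They arise because participants and providers know the treatment, and they would be present even if every child were randomised.

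**Working it through.** **1. The plan's own figure.** Inputs from Sample Size Calculation: "mean 35.89, SD 8.46 laps) and the control group (mean 26.76, SD 10.57 laps", α = .05, power 0.95, 10% loss.

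- Pooled SD = √[(8.46² + 10.57²)/2] = 9.57 laps.
- d = (35.89 − 26.76)/9.57 = 0.954, against the stated 0.953.
- A two-sided two-sample t test (noncentral t) at d = 0.953 needs 30 per group, with power 0.952.
- 30/0.9 = 33.3, rounded up to 34 per group, 68 in total.

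The stated sample size reproduces. The arithmetic is not at fault.

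**2. How self-selection enters the pooled estimate.** Let f be the share of each arm that got there by preference, and b the prognostic difference, in SD, between those choosing exercise and those choosing control. Randomised children contribute no expected difference when there is no true effect, so the pooled bias is f × b. The document gives neither f nor b; both are assumptions here.

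**3. Illustration.** 30 per arm, no true effect, unadjusted two-sided t test on one follow-up value. The last column applies .05/3 = .0167, in case the Bonferroni correction covers the three primary outcomes.

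| f | b | bias f × b (SD) | rejects at .05 | rejects at .0167 |
|---|---|---|---|---|
| 25% | 0.3 | 0.075 | 5.9% | 2.1% |
| 25% | 0.5 | 0.125 | 7.6% | 2.9% |
| 50% | 0.3 | 0.150 | 8.8% | 3.5% |
| 50% | 0.5 | 0.250 | 15.9% | 7.4% |
| 70% | 0.3 | 0.210 | 12.6% | 5.5% |
| 70% | 0.5 | 0.350 | 26.6% | 14.2% |

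At 10% preference the .05 column would read 5.1% to 5.4%. At 70% and b = 0.5 the bias is 0.35 × 9.57 = 3.4 laps, against a planned difference of 9.13 laps.

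**4. What the randomised children alone can say.** With m evaluable children randomised 1:1, the 95% half-width in SD is t(.975, m − 2) × √(4/m).

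- m = 30 (50% preference of 60): 2.048 × 0.365 = 0.75 SD.
- m = 18 (70%): 2.120 × 0.471 = 1.00 SD.
- m = 6 (90%): 2.776 × 0.816 = 2.27 SD.

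At d = 0.953 and 50% preference (15 per arm), randomised-only power is 0.71.

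**The case against.** **The illustration is not the planned analysis.** This stands. The plan is a mixed model over baseline, 3 and 6 months. If its contrast is group-by-time or adjusts for baseline, stable differences in the measured outcome largely drop out, and what remains is different recovery over time and unmeasured factors. The Bonferroni correction may also lower the rates, though the article does not define its family. The table shows the mechanism and a plausible range; it does not predict this trial's error rate.

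**The problem is disclosed.** This stands in part. Limitations says openly that children with a preference were not randomised and calls the study preliminary. Study Design says prospective clinical trial, not randomised trial. A reader might infer that the protocol hides the non-random allocation; it does not. What it omits is selection bias by name, and it leaves the claim in Grouping and Masking uncorrected.

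**Route terms, covariates and sensitivity analyses belong in an analysis plan.** That is fair as to detail, and their absence from an article proves nothing. The point rests on what is stated: an incorrect justification, two descriptions of allocation that do not agree, and one pooled comparison with a sample size built on it.

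**Stronger readings that the document does not support.**

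- A reader might infer that the estimate *is* biased, and in favour of the intervention. Neither size nor direction can be derived.
- A reader might infer that preference allocation rules out balance on age and gender. Frequency matching, or constrained randomisation of the children without a preference, could achieve it. The defensible point is that the two passages disagree.
- A reader might infer that arm sizes are uncontrolled. The plan is 34 per group, and the mechanism is simply not described.
- A reader might infer that only the randomised subset may support any conclusion. At 70% or 90% preference that subset is too small to carry the trial, so this is a trade-off, not a rule.

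**Conclusion.** The point holds in this form. The statement that the scheme keeps the benefits of randomisation is wrong for the children who choose, and the single pooled intention-to-treat comparison is open to confounding by self-selection. The limitations section admits the nonrandomised subset but attributes the wrong biases to it, and the abstract's matching has no counterpart in the grouping section.

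The size is unknown because the share with a preference and the prognostic shift are not given. Under the assumptions shown, the consequence runs from nearly none (6% to 8% rejection at 25% preference) to serious (13% to 27% at 70%), and is smaller if the model adjusts for baseline or the Bonferroni correction spans the three primary outcomes. Whatever the size, a pooled difference would not by itself support the expected statement that effectiveness has been demonstrated.

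**What to change.** 1. Record the allocation route, preference or randomised, for every child at enrolment. It may be impossible to recover later.
2. Include route and the baseline value of the outcome in the primary mixed model, with age and sex, which are already collected. A route term does not remove confounding among the choosers, so step 3 is also needed.
3. Prespecify the randomised-only estimate, with its confidence interval, as a separate analysis. Label the preference-route and pooled estimates as non-randomised, and word conclusions as association unless the randomised estimate supports more.
4. In Grouping and Masking, delete the claim about preserving randomisation's benefits or limit it to the randomised subset.
5. Reconcile the abstract's matching on age and gender with Grouping and Masking, either by describing the matching step or by removing the phrase.
6. Add selection bias to Limitations.

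The practical cost is one data field plus analysis and protocol wording. The scientific cost is larger: the randomised-only interval will be wide, about ±0.75 SD with 30 randomised and ±1.0 SD with 18, and the headline claim becomes weaker. That width reflects how much randomised evidence the design can provide.

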### Intervention

#### Experimental Intervention Program

The experimental group will undergo a baseline assessment using a self-developed questionnaire including demographic and disease information (obtained from hospital records), height, weight, BMI, 6-minute walk distance (6MWD), body composition, grip strength, and Pediatric Quality of Life Inventory version 4.0 (PedsQL 4.0) score. On the basis of the assessment results, a rehabilitation therapist will design a personalized aerobic exercise intervention program, including exercise prescriptions, home exercise routines, physical activity promotion, and daily activity management.

A self-developed digital management system will provide real-time monitoring of exercise logs and deliver tailored exercise strategies. The intensity of aerobic exercise will be adjusted based on individual fatigue levels measured using the Borg fatigue scale. The intervention will be conducted once daily for 30 minutes, 5 days per week over 24 weeks. The digital platform will also offer educational content and personalized information based on the patient’s condition and exercise progress.

#### Outline of the Exercise-Based Digital Therapy

The aerobic digital intervention exercise training program is tailored to participants’ Borg fatigue scale scores, with 3 intensity levels designed to accommodate varying levels of fatigue, as shown in Table 1. Each program requires 30 minutes of exercise per day, 5 days per week for 6 months.

**Table 1 table1:** Exercises included in each program.

Exercises		Description
**Low-intensity program (Borg fatigue score 6-10)**		
	Seated arm stretch	Participants sit upright with their fingers crossed. They straighten their arms and raise their palms above their head. They hold for 30 seconds to feel a stretch in their arms and upper chest.
	Backward arm lift	Participants cross their fingers behind their back with their palms facing each other. They slowly turn their elbows inward (palms outward) while straightening their arms. They lift their arms upward and away from their hips until they feel a stretch in their arms, shoulders, or chest. They hold for 30 seconds, keeping their chest lifted and chin tucked.
	Seated leg stretch	Participants sit on the edge of a chair with one leg extended and the heel on the floor. They place their hand on the opposite thigh for support. They bend slightly forward at the hips until they feel a stretch in the back of the extended leg. They hold for 10 to 15 seconds and then switch legs.
	Supported knee bend	Participants face a wall or stable surface for support. They place their forearm on the wall and rest their head on the back of their hand. They bend one knee and bring it close to the support, keeping the other leg straight. They hold for 30 seconds and then switch legs.
	Heel-to-buttock stretch	Participants hold the top of their right foot with their left hand and gently pull their heel toward their buttocks. They hold for 30 seconds and then switch legs.
	Waist stretch	Participants stand with their feet shoulder-width apart. They cross their left hand over their waist and raise their right hand above their head. They bend their upper body to the left, hold for 15 seconds, and repeat on the opposite side.
**Moderate-intensity program (Borg fatigue score 11-12)**		
	Standing heel lift	Participants stand upright with their feet shoulder-width apart and arms hanging naturally. They lift both heels off the ground, extending their feet fully. They hold for 5 seconds, then lower their heels and repeat 5 times.
	Lunge with arm raise	Participants stand with their feet shoulder-width apart and hands on their hips. They lunge forward with their left leg, bending both knees until their right knee nearly touches the ground. They raise their arms above their head, interlocking their palms. They hold for 15 seconds and then return to the starting position.
	One-legged stand	Participants stand near a wall for support. They lift one foot slightly off the ground, bending the other knee. They hold for up to 30 seconds and then switch legs.
	Back stretch	Participants position themselves on all fours with their hands under their shoulders and their knees under their hips. They arch their back upward, holding for 10 seconds, and then lower their back slightly. They repeat for 30 to 60 seconds.
	Standing shrug	Participants stand with their feet shoulder-width apart, chest up, and core engaged. They let their arms hang naturally at their sides with palms facing in. To perform the movement, they elevate their shoulders toward their ears in a controlled motion, hold the contraction briefly at the top, then slowly lower back to the start.
	Kneeling push-ups	Participants place their hands on the ground slightly wider than shoulder-width apart, with their knees hip-width apart. They bend their elbows to lower their chest toward the ground and then push back up.
**High-intensity program (Borg fatigue score 13-14)**		
	In-place high knee raises	Participants stand with their hands on their waist and upper body straight. They lift their right knee to form a right angle with their thigh and calf and then alternate with their left knee in a running motion.
	Deep squat	Participants stand with their back against a wall and feet slightly apart. They slide down the wall until their thighs are parallel to the floor, keeping their hips higher than their knees. They hold for 5 to 10 seconds and then return to the starting position.
	Knee straightening	Participants sit in a chair with their feet together. They straighten one knee, hold for a few seconds, and then slowly lower it and repeat with the other leg.
	Wall push	Participants place their hands at shoulder height on a wall with their fingers pointing upward. They bend their elbows to bring their body closer to the wall and then push back until their arms are straight.
	Plank support	Participants position themselves on their elbows and toes, keeping their body in a straight line from the shoulders to the ankles, and hold for 30 seconds.
	Step-up squat	Participants stand in front of a sturdy bench with one leg bent back and their toes on the bench. Participants bend their forward leg until their thigh is parallel to the floor and then return to the starting position. Participants complete 10 repetitions and then switch legs.

### Control Group Program

Children with neuroblastoma who meet the inclusion criteria will be introduced to the study’s purpose. After obtaining informed consent, a baseline survey will be conducted using a self-developed questionnaire that includes demographic and disease information extracted from the hospital’s information system. Additional baseline measurements include height, weight, BMI, 6MWD, body composition, grip strength, and PedsQL 4.0 score. The control group will receive standard in-hospital medical treatment and health education. At the 3- and 6-month follow-up visits, outcome assessments and questionnaires are administered to the control group (demographic and baseline disease information are not collected).

### Compliance Supervision

All personnel involved in the study will be qualified and have undergone prestudy training to ensure role clarity and standardization. Data collectors, data entry personnel, rehabilitation therapists, and digital therapy supervisors will complete training and pass examinations to ensure consistency. Participants in the experimental group will be added to a digital management platform (WeChat app) where they will log daily exercise sessions and receive educational content and virtual or physical rewards based on their adherence. A home training diary will be maintained by patients or their guardians on the digital platform to record exercise time and frequency. Quality control personnel will regularly monitor adherence through the platform. Participants who complete the study will receive additional small toy incentives or follow-up program instruction sessions. Adherence to digital therapy will be measured as the percentage of completed daily log-ins relative to the minimum required (80% adherence threshold). Participants with adherence below 80% will be contacted by the researchers to document reasons for noncompliance.

### Withdrawal Criteria

Participants will be withdrawn from the study for the following reasons: (1) serious violation of the test protocol by the participant or their guardian or (2) receipt of other treatments by the participants during the trial that interfere with the study.

### Suspension Criteria

This study will be suspended or terminated for participants under the following circumstances: (1) failure to complete the 6-month intervention as required by the study protocol, (2) occurrence of serious safety issues that compromise participant safety, (3) significant protocol deviations that hinder efficacy or safety evaluation, (4) a decision by the ethics committee to suspend or discontinue the study, or (5) a decision by the study sponsor to suspend or halt the study.

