Aerobic exercise, the most commonly studied form of exercise intervention in oncology, has been shown to enhance cardiovascular fitness, boost metabolism, strengthen muscles, improve quality of life, reduce fatigue, and alleviate depression [15-17]. For instance, Leclerc et al [18] reported significant improvements in motor function, body fat percentage, and quality of life in patients with breast cancer following a 3-month multidisciplinary aerobic exercise program. Similarly, Tanriverdi et al [19] found that a virtual reality–based aerobic exercise intervention improved sleep quality in children with acute lymphoblastic leukemia. Despite these benefits, patient adherence remains a significant barrier to the implementation of exercise interventions. Blanchard et al [20] noted that 52.7% to 70.4% of patients with cancer in the United States fail to meet recommended exercise guidelines. Strategies to enhance adherence and intervention efficacy are critical for advancing this field. For example, Le et al [21] demonstrated that a 12-week telephone-based exercise intervention improved physical activity, fatigue, quality of life, and vitality in survivors of cancer. However, such interventions require substantial manpower and lack direct interaction, highlighting the need for more scalable and interactive solutions.

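### Suspension ground (1) ends the study for children who do not complete the 6-month programme: in practice it acts on the experimental arm only and conflicts with the intention-to-treat analysis

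*Protocol article*

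**What the plan says.** Suspension Criteria in the protocol article gives five grounds. The first is that the study "will be suspended or terminated for participants under the following circumstances: (1) failure to complete the 6-month intervention as required by the study protocol". What ends is the study for that child. Where only treatment is at issue, the article words it differently: Adverse Events and Quality Control and Quality Assurance both speak of stopping or suspending the intervention.

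The Abstract shows who has a 6-month intervention: "the experimental group will receive a 6-month digital therapy–based aerobic exercise intervention in addition to standard care". The outline of the exercise therapy sets the requirement: "Each program requires 30 minutes of exercise per day, 5 days per week for 6 months". For the other arm, Control Group Program says "The control group will receive standard in-hospital medical treatment and health education", with outcome assessments at 3 and 6 months.

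Two other sections bear on the same children:
- Compliance Supervision: "Participants with adherence below 80% will be contacted by the researchers to document reasons for noncompliance". It states no further consequence.
- Statistical Analysis: "Primary models using the intention-to-treat principle will be conducted for all primary and secondary outcomes", with a mixed model over all assessment times.

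Sample Size Calculation allows for loss equally in both groups: "To account for a potential 10% loss to follow-up, 34 participants per group were planned for recruitment".

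**The concern.** Intention to treat needs outcomes from children whether or not they took the allocated treatment. Ground (1) ends participation because a child did not take it as required, and only one arm has a programme that can be failed in this way.

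Children who stop a 6-month exercise programme are plausibly the more fatigued or more impaired. If their week-24 values are not collected (or their week-12 values, if they stop early), the remaining experimental children look fitter than the group that was allocated. The comparison then tilts towards the intervention even if it does nothing. This touches all three primary outcomes, which are physical performance tests. Values never collected cannot be recovered later by analysis.

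There is also a practical conflict. For a child who is logging too few sessions, one section says to make contact and record the reason, while another may end the study for that child. The article does not say where one rule stops and the other begins.

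**Working it through.** **Step 1: the plan's own figure.** Inputs from Sample Size Calculation: means 35.89 and 26.76 laps, SDs 8.46 and 10.57, α = .05, power 0.95, 10% loss.
- Pooled SD = √((8.46² + 10.57²)/2) = 9.573.
- d = (35.89 − 26.76)/9.573 = 9.13/9.573 = 0.954, against 0.953 stated.
- Noncentral two-sample t test, two-sided α = .05, d = 0.953: 30 per group gives power 0.952.
- 30/0.9 = 33.3, rounded up to 34 per group, 68 in total.

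The stated figures reproduce, and this point does not change them.

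**Step 2: whom the rule can reach.** Ground (1) needs a 6-month intervention that can be left incomplete. The Abstract and the therapy outline give one to the experimental group. Control Group Program describes standard treatment, health education and two follow-up assessments, with no programme to complete. Grouping and Masking does speak loosely of a preference between two interventions, so a reading that includes controls is possible. It is the weaker reading, because nothing in the control programme defines completion.

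**Step 3: what is lost.** A child whose participation ends before week 12 contributes only baseline. One who leaves between week 12 and week 24 contributes baseline and week 12. The mixed model uses those values, but it corrects for the missing visits only as far as the observed values explain who stopped.

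**Step 4: possible size.** The article gives neither the fraction who stop nor how strongly stopping relates to outcome, so both are assumed. Further assumptions: no true effect, non-completers absent from the 6-month comparison, all 34 controls present (a simplification), unchanged SD, and less able children stopping first. Let q be the fraction of the experimental arm that stops and ρ the correlation between completion propensity and outcome.
- Bias in SD units = ρ·φ(z_q)/(1 − q), where φ is the standard normal density and z_q its q-quantile.
- Noncentrality = bias/√(1/n₁ + 1/34), with n₁ = 34(1 − q). The two-sided error at nominal .05 follows from the noncentral t distribution.

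Worked case, q = 0.30 and ρ = 0.5: φ(z_q) = 0.348; bias = 0.5 × 0.348/0.70 = 0.248 SD; n₁ = 23.8; noncentrality = 0.248/0.267 = 0.93; error = 15.0%.

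| Stopped (q) | n₁ | Bias, ρ = 0.2 to 0.5 | Two-sided error |
|---|---|---|---|
| 10% | 30.6 | 0.04 to 0.10 SD | 5.3% to 6.7% |
| 20% | 27.2 | 0.07 to 0.17 SD | 5.8% to 10.3% |
| 30% | 23.8 | 0.10 to 0.25 SD | 6.5% to 15.0% |

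On the planning SD of 9.573 laps, the 30% row is about 0.9 to 2.4 laps, against a planning difference of 9.13 laps.

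**Step 5: power.** At d = 0.953 with 34 controls and no bias, power is 0.964 with 10% stopped and 0.939 with 30% stopped. The problem is selection, not numbers.

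**The case against.** The strongest reply is that no section removes non-completers from the analysis. Statistical Analysis promises intention to treat, and the mixed model keeps every visit a child attended. That stands: a reader might infer that the analysed experimental arm is, by rule, a completers' arm, and the article does not say so. But intention to treat cannot use values that were not collected, so the selection arises through missing data rather than through an exclusion rule.

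A reader might also infer that the control arm stays whole. It need not. The Withdrawal Criteria, the other suspension grounds and the planned 10% loss all reach controls. What can be said is that ground (1) adds a further route that acts on one arm.

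Failure to complete is not defined. If it is judged only at month 6, the week-24 visit is already due and little is lost. That is fair, but the text equally allows the rule to be applied when a child stops. Nor does it say whether follow-up ends with the exercise. The contrast with the wording in Adverse Events favours the reading that participation ends.

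Low log-in adherence and failure to complete could be separate triggers, so Compliance Supervision and ground (1) are unreconciled rather than flatly contradictory.

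It is tempting to take the Introduction's figure, that "52.7% to 70.4% of patients with cancer in the United States fail to meet recommended exercise guidelines", as a dropout rate and conclude that power collapses. It describes guideline attainment in another population, not non-completion of a prescribed programme, and supports no such calculation.

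Finally, the error rates above are at nominal .05, whereas the article plans Bonferroni adjustment, and at the only loss rate it gives (10%) the distortion is small.

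**Conclusion.** The point holds as a conflict between provisions with a one-sided consequence. Followed as written, ground (1) ends participation for non-completers, in practice only in the experimental arm, and so undercuts the stated intention-to-treat models. The resulting bias would favour the intervention if the less able children stop.

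Its size is not known. Under the stated assumptions it runs from minor at 10% stopped to 0.10 to 0.25 SD at 30% stopped. The upper end is about a quarter of the planning effect (0.248/0.953 = 0.26). These are values for a plain 6-month comparison; the mixed model would reduce them by an amount that cannot be worked out from the article. The sample size calculation is sound on its own inputs.

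This should be fixed. It does not by itself invalidate the design, because the article does not exclude anyone from the analysis and the loss may turn out small.

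**What to change.** Remove ground (1) as a reason to end study participation. State instead that a child who stops or does not complete the exercise programme stays in follow-up, is invited to the week-12 and week-24 assessments, and is analysed in the allocated group. Any completers-only analysis should be labelled supportive.

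Reconcile Compliance Supervision, Suspension Criteria and Statistical Analysis so that one rule governs non-adherence, with stopping the exercise kept distinct from ending follow-up. The safety and deviation grounds are left to the investigators; nothing here bears on when exercise should stop.

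The cost is protocol wording, since the visits are already in the study timeline, plus some effort to bring non-completers back. The effect estimate will be more diluted because it includes children who did not complete. The change does not remove bias from preference-based allocation, which the article acknowledges under Limitations.
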